#### Data Collection for the PrEP-in-Pharmacy Intervention Arm

Data for the intervention participants will be captured onto a mobile health tool, REDCap (Research Electronic Data Capture; Vanderbilt University) [48], operating on tablets. Built-in eligibility parameters, refill scheduling, and dispensing information, as well as prompts to guide pharmacists and KP program staff through the PrEP refill process, will be programmed. To protect the privacy and confidentiality of the FSWs, at each refill, only data that pertain to the specific refill will be visible to the pharmacists through the refill interface.

#### Pharmacists’ Enrollment to Implement the PrEP-in-Pharmacy Intervention

Pharmacies will be selected to implement the PrEP-in-pharmacy intervention, based on the following criteria, and will be notified. Inclusion criteria for pharmacies participating in the TOPAZ intervention are (1) a valid pharmacy operating license; (2) interest in administering PrEP to SWs in all their diversity, in accordance with professional standards outlined in the written agreement; and (3) the presence of a private room or cubicle within the pharmacy where the HIV testing and PrEP can be provided.

Participating pharmacies will be requested to provide written consent to participate, agreeing to ensure professional, ethical, and respectful conduct toward SWs. All pharmacy personnel that are responsible for administering prescriptions within the pharmacy will undergo a series of mandatory trainings to prepare for implementation, including protocol training and a MoHCC-certified course for HIV testing.

#### Pharmacy Refill Pickup Procedure

TOPAZ intervention participants will present the TOPAZ referral slip or their KP program number to the pharmacy, and the pharmacy personnel will usher them into the private room for study-related activities, including HIV testing and PrEP refills (if eligible). FSWs who test HIV positive will be referred to the KP program for linkage to care.

#### Sample Size and Power Calculations

Data from our previous work indicate that current PrEP retention at 6 months post-PrEP initiation is 14% among FSWs in Harare. With 8 suburbs (4 per arm) and a target enrollment of 25 SWs per intervention suburb (totaling 100 participants in the intervention arm), and assuming an ICC of 0.12, the study will have ≥80% power to detect a 36% increase in PrEP retention—from 14% in the standard-of-care arm to 50% in the intervention arm. Note that this is a pilot trial and, consequently, is only powered to detect large effect sizes. If retention is lower than expected in the comparison group (eg, 10%), we will have at least 80% power to detect a ≥34% increase in PrEP retention. Likewise, if retention is higher than expected in the comparison group (eg, 30%), we will be adequately powered at 80% to detect a ≥38% increase in PrEP retention.

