##### Outcome 3: Patronage for PrEP Services at Pharmacies

FSWs (overall) and FSWs (aged between 18 and 24 years) patronage for PrEP services at pharmacies, defined as the proportion of all PrEP refill pickups (1, 3, 6, and 12) in intervention suburbs occurring at pharmacies, overall and by pickup month.

#### Data Analysis for Aim 2

For retention outcomes at 1, 3, 6, 9, and 12 months, the KP program database will be used to compare the number and proportion of FSWs retained on PrEP as defined earlier by study arm. We will conduct an intent-to-treat analysis to estimate the intervention’s effect using a cluster-based permutation test applied to the individual-level binary outcome (retained on PrEP and not retained on PrEP) using the *cptest* function in the R cvcrand package (or a similar function). The permutation test will be conducted with the same covariates used during the constrained randomization process at the suburb level (expanded from the values of the cluster-level covariates, according to which cluster everyone belongs). This approach will be repeated for the other outcomes. To produce a measure of effect, a Generalized Estimation Equations model will also be constructed to generate a risk difference of PrEP retention among people initiating PrEP in intervention versus comparison suburbs and a 95% CI. In accordance with the CONSORT (Consolidated Standards of Reporting Trials) guidelines, unadjusted estimates will be reported, and the preregistered analysis plan at ClinicalTrials.gov will specify an adjusted model in the case of baseline imbalances. Overall, this analysis framework permits causal attribution.

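### The stated power of at least 80% comes from a large-sample formula that ignores having only 4 suburbs per arm; with the same inputs a 6-df cluster-level test has about 70%, and the planned permutation test less unless covariates help

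*Protocol article*

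**What the plan says.** The section Sample Size and Power Calculations gives these inputs: "a target enrollment of 25 SWs per intervention suburb", 8 suburbs with 4 per arm, and "assuming an ICC of 0.12". For retention rising "from 14% in the standard-of-care arm to 50% in the intervention arm" it states that "the study will have ≥80% power to detect a 36% increase in PrEP retention". If control retention is 10%, "we will have at least 80% power to detect a ≥34% increase in PrEP retention". If it is 30%, "we will be adequately powered at 80% to detect a ≥38% increase in PrEP retention". The increases are percentage points, so the other two scenarios are 10% to 44% and 30% to 68%.

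The section gives no significance level, sidedness, formula or small-sample correction, and no enrolment number for the comparison suburbs. It does warn that a pilot is powered only for large effects.

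The intention-to-treat test is set under Data Analysis for Aim 2: it is made "using a cluster-based permutation test applied to the individual-level binary outcome", with the covariates that constrained the randomisation. A generalized estimating equations (GEE) model is added to give a risk difference and 95% confidence interval. The Aim 2 Overview specifies covariate-constrained randomisation but not the size of the constrained set.

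**The concern.** With 4 suburbs per arm, a cluster-level comparison has 8 − 2 = 6 degrees of freedom for the between-suburb variance. The two-sided 5% critical value is then 2.447 instead of 1.96. A permutation test over at most 70 allocations is coarser still, because only a few p values are possible. A calculation that inflates the individual sample size by a design effect and then applies 1.96 allows for neither.

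At stake is how the Aim 2 result is read. Someone who trusts the 80% figure could take a non-significant result as fair evidence against a 36-point effect, when the test had a much lower chance of detecting it.

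**Working it through.** **Inputs.** From Sample Size and Power Calculations: 4 suburbs per arm, 25 women per intervention suburb, ICC 0.12, and the three pairs of rates. Assumed because the article does not state them: 25 per comparison suburb, and a two-sided 5% level (consistent with the planned 95% interval).

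**Reproducing the stated figure**
- Design effect: 1 + (25 − 1) × 0.12 = 3.88. Effective size per arm: 100 / 3.88 = 25.77.
- For 14% vs 50% the mean rate is 0.32. Pooled SE: √(2 × 0.32 × 0.68 / 25.77) = 0.1299. Unpooled SE: √((0.14 × 0.86 + 0.50 × 0.50) / 25.77) = 0.1199.
- Power = Φ[(0.36 − 1.96 × 0.1299) / 0.1199] = Φ(0.879) = 81.0%.
- The same formula gives 80.4% for 10% vs 44% and 79.7% for 30% vs 68%.
- Solved for 80% power, it gives 33.9, 35.6 and 38.1 points at 10%, 14% and 30% control retention. These round to the stated 34, 36 and 38.
- The other variants tried were noncentral t on 6 or 3 df, one- or two-sided, pooled or unpooled, and the unpooled z. None returns all three stated differences.

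**Cluster-level test on 6 df, same inputs**
- Unpooled noncentrality for 14% vs 50%: 0.36 / 0.1199 = 3.003. Noncentral-t power is 70.8%. The other two scenarios give 70.0% and 69.3%.
- With the pooled SE the noncentrality is 2.770 and power is 63.9%; the others are 63.3% and 62.7%.
- Like for like, the degrees of freedom take the unpooled figure from 85.2% to 70.8%.
- A beta-binomial simulation of a t test on suburb proportions gives about 69%, 69% and 67%.
- Enlarging the comparison suburbs to 1,000 women each lifts 14% vs 50% only to 73.9%.
- Detectable differences at 80% power (unpooled) are 38.7, 40.3 and 42.4 points at 10%, 14% and 30%. With pooled variance they are 43.7, 45.2 and 46.8.

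**Planned permutation test**
- There are at most C(8,4) = 70 allocations. Each has a mirror image with the same absolute difference, so the smallest two-sided p is 2/70 = 0.029 and the next is 4/70 = 0.057. Only the most extreme split is significant. In the unadjusted simulation with 25 per suburb, this coincided with all intervention suburbs lying above all comparison suburbs.
- A constrained set that keeps mirror pairs has smallest p = 2/N: 2/40 = 0.05, but 2/38 = 0.053. Below 40 allocations p ≤ 0.05 cannot occur.

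Simulated power (beta-binomial, ICC 0.12, 25 per suburb in both arms, covariates not prognostic; runs agree to about a point):

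| Allocation set | 14→50% | 10→44% | 30→68% |
|---|---|---|---|
| All 70 | 48% | 50% | 44% |
| 40, average over random sets | 58% | 60% | 54% |
| Fewer than 40 | 0% | 0% | 0% |

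For 14% vs 50%, individual 40-allocation sets ranged from about 51% to 66%. With 200 women per comparison suburb the averages rise to about 55% (70 allocations) and 65% (40 allocations).

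**The case against.** **The permutation figures are conditional.** This stands. The planned test adjusts for the randomisation covariates, and the simulation left them out. The article does not say how prognostic they are, or whether ICC 0.12 is before or after adjustment. As an illustration with assumed values, a residual ICC of 0.06 gives about 67% power with 70 allocations and 75 to 76% with 40; a residual ICC of 0.03 gives 81% and 87%. A reader might infer from the table that the permutation test cannot exceed about 58%, or that it will miss a 36-point effect half the time. Neither follows: 58% is an average under stated assumptions. One artificial 40-allocation set reached 77 to 82%.

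**The variance form matters.** This also stands. The published figure uses pooled variance in the critical value, whereas the 71/70/69% and 39/40/42 points use unpooled variance. Pooled variance makes the 6-df result worse, so the choice favours the plan.

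**A one-sided test or the GEE model might restore the claim.** A one-sided 5% test would have 79 to 84% power on 6 df and about 76% by permutation over 70 allocations. The article states no such test, and that variant does not return its three differences. An uncorrected large-sample z test of the GEE type, approximated on suburb means, shows about 87% power, but with a type I error of about 13%.

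**It is only a pilot.** The caveat about large effects does not help, because 36 points is the large effect in question. The caveat does limit the harm. A reader might also infer that a non-significant p value would block progression. The documents do not support that: the progression rule is a qualitative assessment of four indicators with no p-value threshold, and trial outcomes are one source among several for two of them.

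**Conclusion.** The power statement is wrong as written. At ICC 0.12 and two-sided 5%, power for 14% vs 50% is about 71% on 6 df (64% with pooled variance) if the comparison suburbs also have 25 women each, and at most about 74% with very large ones. The 6-df result does not depend on the allocation set or the covariates. Permutation power cannot be fixed from the article, because the size of the constrained set, the comparison-arm number and the strength of the covariates are not given. About 48% with all 70 allocations and uninformative covariates is a reference value, not a prediction. The defect is in the stated operating characteristics; it does not make the permutation test or the randomisation invalid.

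**What to change.** In Sample Size and Power Calculations:

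- Restate power either for the named permutation test, using the actual size of the constrained set and the actual comparison-arm number per suburb, or for a 6-df cluster-level analysis (about 70% for 14% vs 50%).
- If the permutation test is kept, confirm that the constrained set holds at least 40 allocations, so that p ≤ 0.05 is attainable.
- Replace the detectable differences of 34, 36 and 38 points (10%, 14%, 30% control retention) by about 39, 40 and 42, labelled as 6 df, unpooled variance and 25 per suburb in each arm. If the comparison suburbs differ from 25, recompute them.
- State the significance level and sidedness, and whether ICC 0.12 is before or after covariate adjustment.
- Say that a non-significant result does not rule out a 36-point effect.

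The cost is wording and one short calculation. Data collection ended in May 2025, so enrolment does not change and no participants are added. The stated power becomes less favourable.

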#### Outcomes

##### Outcome 1: Retention on PrEP at 6 Months

This will be measured as attendance within a window of −7 to +7 days of the scheduled 6-month refill visit. Outcome 1 will be expressed as the proportion of 6-month visits completed as scheduled, overall and by arm.

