### Study Aims

The overall goal of the TOPAZ study is to increase PrEP continuation among FSWs through a co-developed pharmacy-based intervention. Specific aims are as follows: aim 1 is to refine and operationalize pharmacy-based PrEP distribution, including an escalating incentive with FSWs and pharmacy owners to motivate PrEP continuation in FSWs; aim 2 is to determine whether the addition of pharmacy-based PrEP distribution increases PrEP retention among FSWs at 6 months compared to standard services; and aim 3 is to understand the PrEP-in-pharmacy program’s potential to scale and translate lessons learned into a future effectiveness study.

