#### Overview of PrEP Services in the KP Program

The KP program requires verbal consent from SWs to dispense PrEP, which is freely available [5]. MoHCC implementation guidelines include free provider-delivered oral rapid HIV testing at initiation, along with provision of a 1-month supply of PrEP. The first refill provides a 2-month supply of PrEP, followed by 3-month supplies for subsequent refills (Figure 4). Free, provider-delivered oral rapid HIV testing will be offered every 3 months, and in accordance with the national PrEP guidelines, only individuals with confirmed HIV-negative results are offered future PrEP refills [47]. KP program data are collected on paper-based forms for all SWs who initiate PrEP routinely; these are used to generate a unique identification number for the SWs and an associated KP program file, which is essential for PrEP refill collection. People who do not return for refill visits are routinely followed up via phone calls, WhatsApp (Meta Platforms, Inc) reminders, and peer outreach. SWs are offered a US $5 transport reimbursement when collecting their PrEP refills routinely in the program.

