#### Procedures for the Standard-of-Care Arm

SWs enrolled as part of the TOPAZ study in the standard-of-care arm will initiate PrEP following the KP program standard operating procedures. They will be recruited through the KP program outreach clinics; undergo HIV testing; and if they are HIV negative, they provide verbal consent for PrEP initiation and collection of subsequent refills. At each visit, SWs will receive PrEP plus counseling on the importance of adhering to the prescribed PrEP schedule. PrEP refills will be recorded on standardized paper-based data collection tools, per the KP program standards, and will be analyzed from the program records.

Inclusion criteria for enrollment into the TOPAZ standard-of-care arm are (1) initiated on PrEP through the KP program’s mobile outreach clinics operating in 1 of the 4 standard-of-care suburbs, (2) aged >16 years, (3) having exchanged sex for money in the last 6 months, and (4) providing verbal consent.

All participants will receive a US $5 transport reimbursement at the end of each visit. Participants in the standard-of-care arm will be advised that they can collect PrEP refills from the KP program clinics, following standard procedures. Participation in the intervention will continue for 12 months.

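### The 7-day window makes 6-month retention a mix of continuing PrEP and collecting it on time, so arms with equal continuation could differ on it

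*Protocol article*

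**What the plan says.** - **Aim.** Under Study Aims, aim 2 is to "determine whether the addition of pharmacy-based PrEP distribution increases PrEP retention among FSWs at 6 months compared to standard services".
- **Definition.** Under Outcome 1: "This will be measured as attendance within a window of −7 to +7 days of the scheduled 6-month refill visit", and "Outcome 1 will be expressed as the proportion of 6-month visits completed as scheduled, overall and by arm". Outcome 2 applies the same window to women aged 18 to 24.
- **Analysis.** Data Analysis for Aim 2 uses the program database to "compare the number and proportion of FSWs retained on PrEP as defined earlier by study arm". A permutation test and a risk difference are then applied to a binary retained/not-retained variable.
- **Supply.** Under Overview of PrEP Services in the KP Program, initiation comes with one month of drug. After that, "The first refill provides a 2-month supply of PrEP, followed by 3-month supplies for subsequent refills". Women who miss a refill are traced by phone, messaging and peer outreach.
- **Arms.** "Participants in the standard-of-care arm will be advised that they can collect PrEP refills from the KP program clinics". Intervention participants can use those clinics or selected pharmacies in the suburb. Pharmacy refills at months 1, 3 and 6 also earn a voucher, worth US $7 at month 6.
- **What the article does not give.** It states no wider window and no supply-based measure. The limitations under Anticipated Findings call refills a measure of continuation and do not mention the window.

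**The concern.** The outcome is named retention but scored by date. A woman whose 6-month refill falls 8 or more days from the scheduled date, on either side, gets the same code as a woman who gave up PrEP.

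If that miscoding were equally common in both arms, it would mainly dilute the comparison. It need not be equal here. Extra collection points and a voucher tied to the scored visit are features that can change when women collect, apart from whether they continue. The article's own theory section presents the incentive as a remedy for present bias in refill collection, so an effect on timing is plausible.

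Aim 2, the abstract's promise to report on PrEP continuation, and the statement that the framework allows causal attribution all depend on this variable. An effect on timing could therefore be reported as an effect on continuation. A real gain in continuation could also be hidden if pharmacy users collect less close to the scheduled date.

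**Working it through.** **1. The plan's own figure.** The sample size section gives 4 suburbs per arm, 25 women per intervention suburb, ICC 0.12, and at least 80% power for 14% vs 50%. I assume equal arms and two-sided 5%, since neither is stated.
- Design effect = 1 + (25 − 1) × 0.12 = 3.88.
- Effective n per arm = 100 / 3.88 = 25.8.
- The pooled normal approximation gives power of 81.0%.

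The stated power reproduces and is not in dispute. The effective n is used again in step 5.

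**2. Supply against the window.** Supply is 1 month at initiation, 2 months at the month-1 refill and 3 months at the month-3 refill. 1 + 2 + 3 = 6 months, so for a woman who kept to schedule it runs out at about the 6-month visit.

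| Actual behaviour | Supply if earlier refills were on schedule | Coded |
|---|---|---|
| Refills 8 or more days early | Unbroken | Not retained |
| Refills within 7 days either side | About unbroken | Retained |
| Refills 8 or more days late, continues | Probably lapsed, then resumed | Not retained |
| Stops | Ended | Not retained |

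The first row is a clear misclassification as a measure of retention. The third is debatable.

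**3. Structure of the bias.** Let c be true continuation, equal in both arms, and s the share of continuers who attend inside the window. Scored retention is c × s, so the scored difference is c × (s for intervention − s for comparison). It is zero only when the on-time shares are equal, and it takes the sign of the difference between them.

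**4. Size, by assumption.** The article gives no pickup-date data. Assume normal deviations centred on the scheduled date, with limits at 7.5 days as a continuity correction.
- SD 5 days: s = 0.866.
- SD 7 days: s = 0.716.
- SD 10 days: s = 0.547.

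| Equal continuation c | SD 5 vs 10 days | SD 7 vs 10 days |
|---|---|---|
| 40% (assumed) | 0.40 × 0.319 = 12.8 points (34.7% vs 21.9%) | 0.40 × 0.169 = 6.8 points |
| 14% (the design baseline, treated as true continuation) | 0.14 × 0.319 = 4.5 points | 0.14 × 0.169 = 2.4 points |

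The article does not say whether the 14% was itself scored with a 7-day window, so its use as true continuation is also an assumption.

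The sign can reverse. At 50% continuation, on-time shares of 70% (comparison) and 90% (intervention) give 35% vs 45%, or +10 points. Swapping the shares gives −10.

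**5. Would it be declared significant?** For 34.7% vs 21.9% with effective n 25.8 per arm:
- Pooled standard error = √(2 × 0.283 × 0.717 / 25.8) = 0.125.
- Unpooled standard error = 0.124.
- Power = Φ[(0.128 − 1.96 × 0.125) / 0.124], about 17%.

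That is above 5%, but a gap of this size would usually not reach significance in this pilot. It would still shift the reported risk difference.

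**The case against.** The strongest reply is that the window is a legitimate choice. Supply runs out at about the scheduled date, so a woman more than 7 days late has probably had a gap. Coding her as not retained is defensible as a measure of continuous supply. This stands for late collectors, and any wider late limit is equally a judgement. It does not cover early collectors.

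A second reply is that supporting windows are usual analysis-plan content, and the article points to a registered plan that is not shown. Such an analysis may exist there. The point here concerns the definition that the article itself fixes and what can be concluded from it alone.

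Third, retention is also compared at months 9 and 12, so a woman late at month 6 may be counted later. This helps only in part. The article does not say whether later dates are reset after a late refill, and aim 2 is stated at 6 months. Progression to a larger trial is a qualitative traffic-light judgement, which also limits the damage.

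Readers might infer three stronger things that the document does not support:
- **That the outcome measures punctuality only.** It does not: women who stop also score zero.
- **That comparison women depend on infrequent mobile clinics.** Both arms are recruited at mobile outreach clinics, the program also runs static clinics, and no clinic frequency is given.
- **That a positive result would be spurious.** No on-time data are given, and the bias could run either way.

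**Conclusion.** The point holds in this form: the stated 6-month outcome combines continuing PrEP with collecting it near a set date, and the article offers nothing to separate the two. Because the arms differ in features that may affect timing, a risk difference on this outcome cannot by itself be read as a difference in continuation.

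The size is unknown. The illustrations of 7 to 13 points at 40% continuation and 2 to 5 points at 14% rest on assumed pickup SDs, equal true continuation and dates centred on schedule. They are small beside the 34 to 38 point differences for which the trial is powered. The case is therefore for protecting the interpretation, not for replacing the outcome.

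**What to change.** Keep the 7-day measure as the protocol-defined outcome. Before the comparative analysis, which the article schedules for February 2026, specify the following:

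1. One supporting 6-month analysis from the same dispensing dates, applied identically in both arms, that credits early refills and uses a wider late limit. Thirty days is an example, and it should be labelled a judgement because supply may have lapsed by then.
2. A table of days early or late by arm among women who refilled.
3. A reporting rule: if the risk difference is materially smaller under the wider definition, describe the result as on-time refill collection rather than continuation. State beforehand what counts as materially smaller. If the difference is larger, say that the 7-day rule understated it.

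No new data should be needed, since the 7-day rule cannot be scored without visit dates in both arms. The cost is a second retention figure to report and explain. It must be labelled as specified after data collection ended in May 2025.
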